### **7.3 Safety analysis**

Adverse events that occur during this study will be presented by system organ class (SOC), high level term (HLT), and preferred term (PT) in a frequency table giving the number of events, the number of subjects, and the percentage of subjects who experience the event by treatment group.

Subjects with multiple AEs will be counted only once within each PT, HLT, and SOC.

Coding of the AEs will be performed with the Medical Dictionary for Regulatory Activities.

### **7.4 Handling of protocol deviations**

The clinical project manager will prepare the Specification of Protocol Deviations in consultation with the Clinical Trial Biostatistician and Study Physician. Search criteria for potential protocol deviations will be detailed in the Specification of Protocol Deviations. During the blind period, the protocol deviations will be classified according to their impact on the primary objective.

All important protocol deviations, including missing relevant data, will be listed by subject.

### **7.5 Handling of dropouts or missing data**

Rules for imputation of missing data will be detailed in the SAP. When analyzing efficacy data, if the missing data is type MAR (Missing At Random) or MCAR (Missing Completely At Random), a multiple imputation will be implemented.

## **8. Assessment of Safety and Tolerability**

Safety and tolerability will be evaluated by recording adverse events (AEs) and serious AEs (SAEs) throughout the study, on all patients enrolled in the study. Number of participants with adverse events, type of adverse event and their repartition between treatment arms will be used as a measure of safety and tolerability.

### **8.1 Safety parameters**

The following parameters will be assessed and analysed for study product safety:

- clinical review and questionnaires for pain,
- disability and quality of life at 0, 6 12 and 24 months
- physical examinations performed at baseline , M3, M6, M12 and M24 after injection of the cells;
- laboratory tests (haematology, blood chemistry) and vital signs assessed at baseline, M1, M3, M6, M12 and M24. Elevations in ALT and/or AST  $>3 \times$  ULN will also be reported since this level was considered to be most relevant to health authorities and healthcare providers.

### **8.2 Definition**

#### *Adverse Event :*

An adverse event is any untoward medical occurrence in a patient or clinical investigation subject administered a pharmaceutical product and which does not necessarily have to have a causal relationship with this treatment. An adverse event (AE) can therefore be any unfavourable and unintended sign (including an abnormal laboratory finding, for example), symptom, or disease temporally associated with the use of a medicinal product, whether or not considered related to the medicinal product.

An adverse event, whether or not considered to be the causally related to the investigational medicinal product, may be:

The deterioration of a pre-existing chronic disease or aggravation of a symptom or disease that was present on enrolment of the patient in the study

A symptom or disease discovered after the start of the study even if it was probably present prior to the patient's enrolment in the study.

Abnormal laboratory findings will be considered as adverse event when they are considered /judged as clinically significant by the investigator.

Clinically significant event/value should be defined as: symptomatic, requiring corrective treatment, leading to discontinuation, dose delay, dose reduction, dose interruption and/or fulfilling seriousness criteria.

#### Adverse drug reaction (ADR)

All noxious and unintended responses to a medicinal product related to any dose should be considered adverse drug reactions.

An adverse reaction is an AE that is at least possibly related to the administration of the study medication or procedure. When assessing the relationship ("related" or "unrelated") between an AE and the study medication or procedure, the following points should be taken into consideration:

- close timely relationship between administration of study medication or procedure and occurrence of AE
- information about the side effect profile of the study medication or procedure from non-clinical and clinical studies
- mechanism of action of study medication or procedure potentially explaining the occurrence of the AE
- other factors with causal potential
- impact of concurrent therapeutic or diagnostic measures
- personal physical or psychological stress factors on the participant's side

#### Serious adverse event (SAE)

A SAE is an AE with at least one of the following characteristics:

- results in death
- is life-threatening
- requires inpatient hospitalization or prolongation of existing hospitalization
- results in persistent or significant disability or incapacity
- is a congenital anomaly or birth defect
- is an important medical event

NOTE: The following hospitalizations are not considered SAEs:

- a visit to the emergency room or other hospital department lasting less than 24 hours that does not result in admission (unless considered an "important medical event" or a life-threatening event)

- elective surgery planned before signing consent
- admissions as per protocol for a planned medical/surgical procedure
- routine health assessment requiring admission for baseline/trending of health status (eg, routine colonoscopy)
- medical/surgical admission for purpose other than remedying ill health state that was planned before study entry. Appropriate documentation is required in these cases.
- admission encountered for another life circumstance that carries no bearing on health status and requires no medical/surgical intervention (eg, lack of housing, economic inadequacy, caregiver respite, family circumstances, administrative).

### Serious adverse reaction (SAR)

A SAR is an AE which is at least possibly related to the study medication or procedure and fulfils at least one of the criteria of seriousness listed above.

A suspected expected serious adverse reaction (SESAR) during a clinical trial is an AE which is at least possibly related to the study medication or procedure, fulfills at least one of the criteria of seriousness listed above and is listed as potential side effect of the study medication or procedure in the Summary of Product Characteristics or the Investigators' Brochure.

A suspected unexpected serious adverse reaction (SUSAR) during a clinical trial is an AE which is at least possibly related to the study medication, fulfils at least one of the criteria of seriousness listed above and is not listed as potential side effect of the study medication or procedure in the Summary of Product Characteristics.

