## 1.6 Risk-benefit assessment

This study will progress beyond the current state of the art as it will be the one of the first clinical trial to reach significance in assessing autologous BM-MSC for the treatment of IDD. This study provides the first major step in determining subsequent clinical and commercial activity relating to stem cell therapy. It will definitively

provide robust in patient regenerative medicine research that either supports or refutes the potential of intradiscal injection of BM-MSC for the treatment of LBP due to IDD grade 3-4 modified Pfirrmann and grade 3-7 Griffith grading system at different levels (max. 3 levels). If successful, this will allow a new therapy to be taken to the next level of testing, taking the field closer to marketability and delivery, a key step that has eluded stem cell therapies to date.

Based on previous clinical experience with similar products reported in the literature, BM-MSC is deemed to be effective and safe in various diseases. Manufacturing of the study medication is performed according to GMP standards. The risk of local or systemic infection, bacteremia, or sepsis due to contamination of the cell preparation seems negligible. Pre-clinical *in vitro* and *in vivo* evaluations of the study medication did not show any hint of tumorigenic potential of the preparation or systemic migration of BM-MSC after intra-discal injection. There is a low risk of systemic AEs occurring after the end of the observation period, but the sample size of this clinical trial implies a very low probability of detecting rare events anyway. At last, procedure related adverse events such as of infections, bleedings, nerve irritations and nerve injuries with its possible consequences paresthesia and paralysis are very rare as the injection are performed using the fluoroscopy to guide the surgeon, but patients will be informed.

The benefit for patients with chronic LBP may be considerable, since BM-MSC might represent the first disease-modifying therapeutic option for this chronic and debilitating disease. Furthermore, under certain pre-defined conditions, e.g. the occurrence of suspected unexpected serious adverse reactions (SUSARs), the Sponsor will suspend treatment of subjects until a decision whether to continue the clinical trial or not has been taken. In conclusion, subjects will be exposed to limited risks during their participation in this clinical trial.

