## **8.3 Expected adverse reactions**

Reference safety document: The current Investigator brochure will be considered as the reference safety document.

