### Expected Adverse Reaction related to injection of autologous bone marrow mesenchymal cell (undetermined frequency, not severe except for immunological reaction)

- transient lumbar pain
- elevation of the body temperature (>37,5°C)

- shivering
- pruritus

*Expected Adverse Reaction related to local intra-discal injection*

- headache and nausea (undetermined frequency, not severe) The following adverse reactions are severe but rare
- local infection (discitis),
- reherniation in operated segments,
- exacerbation of pain, back pain, ischialgia, sciatica, pain in extremity,
- facet joint syndrome,
- meningitis,
- epidural abscess,
- arachnoiditis,
- intrathecal hematoma,
- retroperitoneal hematoma,
- cauda equina syndrome,
- acute disc herniation,
- paralysis,
- cerebrospinal fluid leak.

*Expected Adverse Reaction related to the concomitant medication*

Cf. the current Summary of Product Characteristics (SmPC) to the product.

*Expected Adverse Reaction related to MRI*

Panic attack

*Expected Adverse Reaction related to local  
anesthesia*

- Related to local anesthetic or antiseptic :

Cf. the current Summary of Product Characteristics (SmPC) to the product (1% xylocain for local anesthetic, and chlorhexidine for antiseptic)

- Related to the procedure/technique of local anesthesia:

Anesthesia failures and insufficiencies

Hematomas and arterial dissections

Infections

Neurological lesions (traumatic nerve location or intraneural injection or injected solution toxic)

Error on injected product (Ex: antiseptic, physiological saline)

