## 8.6 Sponsor responsibilities

### Serious Adverse Event and new event

The relation between the event and the study drugs should be evaluated by the sponsor. The sponsor will evaluate whether the events are expected or unexpected.

The sponsor will report any SUSAR and new events according to the legislation and good clinical practice. Any Serious Adverse Reaction related to injection of allogeneic bone marrow mesenchymal cell, to graft rejection of allogeneic bone marrow mesenchymal cell, to local intra-discal injection and those related to bone marrow donation will be declared to the corresponding national competent authority in the same way that SUSARs Regulatory declaration is made within a maximum of:

- without delay for serious adverse unexpected fatal or life-threatening. In this case, additional relevant information should be sought and passed within a further period of 8 days.
- 15 calendar days for all other serious unintended effects. The same additional relevant information should be sought and transmitted in a further period of 8 days.

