### **8.7 Data and Safety Monitoring Board**

No independent data monitoring committee has been appointed for this study.

No formal interim statistical analysis will be performed.

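### Section 8.2 lets one serious reaction be both expected and unexpected, and leaves another unclassified; section 8.6 names an allogeneic product that this trial does not use

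*Protocol*

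**What the plan says.** Section 8.2 sets two classes of serious reaction. A suspected expected one (SESAR) must be at least possibly related to the study medication or a procedure, and be listed "in the Summary of Product Characteristics or the Investigators' Brochure". A SUSAR "is an AE which is at least possibly related to the study medication, fulfils at least one of the criteria of seriousness", and it "is not listed as potential side effect of the study medication or procedure in the Summary of Product Characteristics". The second definition omits the Brochure from the listing test and omits procedures from the relatedness test.

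Section 8.3 then states: "The current Investigator brochure will be considered as the reference safety document". It refers to an SmPC only for concomitant medication, the local anaesthetic and the antiseptic. The cells are described through an investigational product dossier (section 2.1) and the Brochure (section 13.3.2). Section 8.3 also lists 13 entries as severe but rare expected reactions to the intra-discal injection, among them discitis, meningitis and paralysis.

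Section 8.6 requires some serious reactions to be declared to the authority as SUSARs are. It begins "Any Serious Adverse Reaction related to injection of allogeneic bone marrow mesenchymal cell, to graft rejection of allogeneic bone marrow mesenchymal cell" and goes on to intra-discal injection and marrow donation. Section 2.1 says that the cells are autologous, and section 5.8 rules out rejection.

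Section 1.6 says that under certain conditions, for example "the occurrence of suspected unexpected serious adverse reactions (SUSARs), the Sponsor will suspend treatment of subjects until a decision" on continuation has been taken. Section 8.7 adds: "No independent data monitoring committee has been appointed for this study". It also rules out a formal interim analysis.

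**The concern.** Expected and unexpected should exclude each other and, between them, cover every serious reaction. Here they rest on different reference documents and different relatedness tests, so they can do neither. Section 8.6 leaves the expectedness judgement to the sponsor. Two people at the sponsor could each follow the protocol and classify the same event differently.

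Two things depend on the label: SUSAR reporting under section 8.6, and the only worked example of a condition for suspending treatment, in section 1.6. That example supports the statement that participants face limited risks. Section 8.6 also has a clause that could have made the label matter less, but part of it describes a different product.

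**Working it through.** No arithmetic applies; the check sets the clauses side by side.

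**Step 1: the 8.2 definitions.** Inputs: both definitions in 8.2, the reference document named in 8.3, and the absence of any cited SmPC for the cells. Every row below is a serious reaction.

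| Possible cause | In the Brochure? | Meets SESAR wording? | Meets SUSAR wording? |
|---|---|---|---|
| Cells | Yes | Yes | Yes, because no SmPC lists it |
| Cells | No | No | Yes |
| Procedure only | Yes | Yes | No, because not related to the medication |
| Procedure only | No | No | No, for the same reason |

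The first row gets two labels and the last gets none. The middle rows behave as intended.

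**Step 2: who falls in those rows.** The 13 severe entries in 8.3, such as discitis or paralysis, fall in the first row if two conditions hold: the Brochure lists them as 8.3 does, and the cells are at least a possible cause. If the needle alone is blamed, they move to the third row and are SESARs only. The last row includes unlisted serious reactions to the marrow harvest alone, to the sham harvest (section 5.2) and to the sham muscle puncture (section 5.6). Control patients receive no cells, so none of their procedure reactions can meet the SUSAR wording.

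**Step 3: what 8.6 covers.**
- Allogeneic cells: nobody in this trial receives them.
- Allogeneic graft rejection: cannot occur with these cells, by section 5.8.
- Intra-discal injection: applies, and reaches discitis or paralysis attributed to the injection under either label.
- Marrow donation: could be stretched to the patient's own harvest, but not to a sham in which no marrow is taken.

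An expected serious reaction attributed to the autologous cells themselves is not named. The group is small: the reactions to the cells that 8.3 lists are transient lumbar pain, raised temperature, shivering and pruritus, under a heading that calls them not severe apart from immunological reaction.

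**Step 4: section 1.6.** On the literal 8.2 wording, a first-row event is a SUSAR and falls under the suspension example. With the Brochure as the reference under 8.3, it is expected and does not. The protocol does not say which reading governs.

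**Step 5: after aligning 8.2.** With the Brochure as the sole reference and relatedness to medication or procedure in both definitions, rows one and three become SESAR only and rows two and four SUSAR only. Each event then has exactly one label.

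**The case against.** The strongest reply is that little reporting is lost. The intra-discal clause in 8.6 secures SUSAR-type declaration of injection-related discitis, meningitis or paralysis whatever the label. An unlisted serious reaction to the cells is a SUSAR under either document. Because the cells are given only by intra-discal injection, that clause plausibly reaches many cell reactions too. The expedited-reporting list in 8.6 adds increased rates or changed character of expected serious reactions when judged clinically important, and procedure-associated serious events that could change the conduct of the trial. Section 8.5 requires notice of serious events to the sponsor within 24 hours, with listed exceptions. Section 8.3 does name a reference document, and 8.6 ties SUSAR reporting to legislation and good clinical practice.

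Most of this stands, and it limits the consequence. A reader might infer that discitis or paralysis would escape expedited reporting; the intra-discal clause shows otherwise. A reader might also infer that no expected reaction could ever pause the trial. Section 1.6 offers SUSARs only as an example, so that does not follow.

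The reply does not remove the contradiction within 8.2, the unlabelled procedure reactions or the wrong product in 8.6. The extra reporting routes rely on judgement and carry no suspension provision.

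**Conclusion.** This is an internal inconsistency in operative safety wording, and it should be corrected. Two of the four cause-by-listing combinations in 8.2 go wrong, one labelled twice and one not at all, and part of the 8.6 clause describes a product outside this trial. The consequence is conflicting classification and an undetermined status under the suspension example in 1.6. No numerical size attaches to a defect of definition.

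The conclusion rests on two assumptions. First, no SmPC exists for the cells; this is inferred from the protocol citing none. Second, for the discitis and paralysis examples, the Brochure, which is not at hand, lists them as 8.3 does. The procedure gap and the allogeneic wording depend on neither assumption.

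**What to change.** - **Section 8.2:** test SESAR and SUSAR against the one reference document that 8.3 names, and use the same relatedness wording, medication or procedure, in both.
- **Section 8.6:** name the autologous product in place of the allogeneic one, remove the graft-rejection wording, and replace marrow donation with the autologous harvest and its sham counterpart.
- **Section 1.6:** reconcile with 8.2 and 8.3, so that the text says whether reactions listed as expected fall under the suspension provision. That choice belongs to the sponsor, and no rule is proposed here.

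The cost is a wording amendment, with no added patients, visits or data. The change is not neutral. Testing against the Brochure narrows the SUSAR class, because Brochure-listed events leave it and so leave the example in 1.6; 1.6 should therefore be settled in the same amendment. The 8.6 edit and the added procedure wording may in turn produce a few more expedited reports.

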### New events

A new fact is defined as any new safety data, which could lead to a reassessment of the risk/benefit balance of the study or of the investigational product or that could be sufficient to consider changes in the drug administration or in the pursuit of the study

## **8.3 Expected adverse reactions**

Reference safety document: The current Investigator brochure will be considered as the reference safety document.

### Expected Adverse Reaction related to injection of autologous bone marrow mesenchymal cell (undetermined frequency, not severe except for immunological reaction)

- transient lumbar pain
- elevation of the body temperature (>37,5°C)

- shivering
- pruritus

*Expected Adverse Reaction related to local intra-discal injection*

- headache and nausea (undetermined frequency, not severe) The following adverse reactions are severe but rare
- local infection (discitis),
- reherniation in operated segments,
- exacerbation of pain, back pain, ischialgia, sciatica, pain in extremity,
- facet joint syndrome,
- meningitis,
- epidural abscess,
- arachnoiditis,
- intrathecal hematoma,
- retroperitoneal hematoma,
- cauda equina syndrome,
- acute disc herniation,
- paralysis,
- cerebrospinal fluid leak.

*Expected Adverse Reaction related to the concomitant medication*

Cf. the current Summary of Product Characteristics (SmPC) to the product.

*Expected Adverse Reaction related to MRI*

Panic attack

*Expected Adverse Reaction related to local  
anesthesia*

- Related to local anesthetic or antiseptic :

Cf. the current Summary of Product Characteristics (SmPC) to the product (1% xylocain for local anesthetic, and chlorhexidine for antiseptic)

- Related to the procedure/technique of local anesthesia:

Anesthesia failures and insufficiencies

Hematomas and arterial dissections

Infections

Neurological lesions (traumatic nerve location or intraneural injection or injected solution toxic)

Error on injected product (Ex: antiseptic, physiological saline)

#### **8.4 Unblinding procedure**

This trial is a double blind clinical study for both patient and investigator in charge of the patient evaluations. The knowledge by investigator of the treatment administrated in the study may be necessary but should be exceptional and justified in case of SAEs or specific situations by the adaptation of patient care and medical care depending on the treatment received

SAEs and / or situations that could justify unblinding request on medication administrated as part of the protocol are defined below:

- a. Infections requiring hospitalization and administration of IV antibiotics:
- b. Unexplained or possibly toxic death.
- c. Request by health professional (emergency room, intensive care ...) not involved in the study, the patient himself or his entourage in an immediate emergency.

Concerned patient by unblinding procedure will not be withdrawn of the study

#### **8.5 Investigator responsibilities**

##### AEs

Complete and appropriate data on all AEs (only clinically significant event or value) experienced during the clinical trial should be recorded on the AE form of the CRF on an ongoing basis for the duration of the study. Each AE report shall include a description of the event, an assessment of its seriousness according to the criteria listed above, its duration, intensity, relationship to the study medication, other causality factors (if any), any concomitant medication dispensed, actions taken with the study drug or other therapeutic interventions and outcome at the end of the observation period.

The adverse events will be encoded and graded according to CTCAE Criteria Grade 1-5

(Common Terminology Criteria for Adverse Events). A copy of the CTCAE Version 5.0 can be downloaded from the CTEP homepage (<http://ctep.info.nih.gov>). If there is no CTCAE grading possible, the intensity of the adverse event has to be classified in categories:

- Mild (Grade 1) – transient or minimal symptoms; no change in activity or need of medication
- Moderate (Grade 2) – symptomatic; moderate change in activity; no reduction in social activities

- Severe (Grade 3) – incapacitating; bed rest required; loss of work; reduction in social activities
- Life threatening (Grade 4) – significant clinical intervention or hospitalization required
- Fatal (Grade 5)

For each AE, a separate AE form will be filled in.

Follow up of AEs: AEs will be followed until their resolution or stabilisation. However, the observation period will be cut off after the last patient has finished his final visit (LPLV). During monitoring visits, the study monitor will assess accuracy and completeness of all AE forms generated since the last visit by 100% source data verification. Cases of AEs reported earlier for which the outcome is still pending will be checked for new data and developments. Furthermore, queries on AEs reported earlier will be solved with the Investigator. AEs will be reported in the final study report.

The sponsor must be informed immediately of the occurrence of any AE grade 3-4-5 by the associated centre.

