#### **2.4.2 Secondary Endpoint:**

- To evaluate changes of the treated IVD induced by regenerative therapy by quantitative Magnetic Resonance Imaging (MRI) signal measurements in T2, T1spin/echo, and T1rho weighted images that allow a quantitative measure of the NP extracellular matrix.
- To evaluate modification of disability (ODI) and quality of life (SF-36 scores) considered as continuous measures, between baseline and 1, 3, 6, 12 and 24 months.
- Safety and tolerability will be evaluated by recording adverse events (AEs) and serious AEs (SAEs) throughout the study till 24 months. Number of participants with adverse events, the correlation of the AE to the IMP and their severity will be used as a measure of safety and tolerability.
- To evaluate consumption of medications to relieve pain such as type and dose of analgesics will be evaluated. Paracetamol (acetaminophen) and levels 2 analgesics will be assessed throughout the study at each visit.

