### **5.7 Post-treatment care**

The patient is discharged after an observation period of 2 hours. Walk for moderate periods is authorized. Labor activity is suspended for one week. The pain medication is tailored to the needs of each patient and the use of NSAIDs should be avoided. The longterm monitoring will consist of out-patient visits and MRI.

The patients are followed for 2 years on clinical examination, spine MRI. For 2 years they will be followed annually on clinical basis to assess any unexpected long term side effect.

In case the patient have not responded after end of study (3 years) or relapse, he may be eligible for cell therapy when the product will be available on routine basis, or benefit for treatment recommended by EULAR (physiotherapy, steroid or surgery)

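### The fallback severity scale in 8.5 defines its life-threatening grade by intervention or hospitalisation, with no threat to life required, which conflicts with 8.2

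*Protocol*

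**What the plan says.** Protocol 8.5 (AEs) makes CTCAE the rule: "The adverse events will be encoded and graded according to CTCAE Criteria Grade 1-5". A second scale applies only by exception: "If there is no CTCAE grading possible, the intensity of the adverse event has to be classified in categories". Its Grade 4 is labelled life-threatening and described solely as "significant clinical intervention or hospitalization required". Its Grade 3, labelled severe, reads "incapacitating; bed rest required; loss of work; reduction in social activities".

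Protocol 8.2 (Serious adverse event) lists threat to life as one criterion and, as another, "requires inpatient hospitalization or prolongation of existing hospitalization".

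Protocol 2.4.2 brings severity into the safety endpoint: besides the number of participants with events, "the correlation of the AE to the IMP and their severity will be used as a measure of safety and tolerability". Section 8.5 also requires each AE report to give seriousness (by the 8.2 criteria) and intensity as separate items.

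**The concern.** An intensity scale should say how bad the event was. Seriousness criteria say what it led to or threatened. The fallback Grade 4 uses a consequence, admission or intervention, as its test and then attaches a label that asserts danger to life. Section 8.2 keeps these two ideas apart.

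If the rule is followed as written, a patient admitted without any danger to life is entered as having had a life-threatening event. Severity is a named safety measure, so the label can reach the safety results. In a trial of 26 patients per arm, even a few such entries would show in a count of life-threatening events. A later analysis plan cannot repair this from the grade alone, because the definition is applied when the event is recorded.

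**Working it through.** There is no figure in the plan to reproduce, so the check sets the sections side by side and follows one event through them.

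**The two definitions**

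| Question | 8.5, fallback scale | 8.2, seriousness |
|---|---|---|
| What makes an event life-threatening? | Significant intervention or hospitalisation, either one being enough | The event threatens life |
| Where does hospitalisation sit? | Inside the life-threatening grade | A separate criterion |

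**One event, step by step.** Take an event with no available CTCAE grade. The patient is admitted for observation and is at no point in danger.

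1. CTCAE grading is not possible, so 8.5 sends the event to the fallback scale.
2. Hospitalisation was required. The Grade 4 descriptor joins its two conditions with *or*, so this alone meets it. Recorded intensity: Grade 4, life-threatening.
3. Under 8.2 the threat-to-life criterion is not met and the hospitalisation criterion is. Recorded seriousness: serious because of hospitalisation, not life-threatening.
4. Section 8.5 asks for both items on the same report. The two entries disagree on whether life was threatened, yet each follows its own rule. Source data verification of AE forms, set at 100% in 8.5, would not remove the conflict, since neither entry is a transcription error.

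The same happens at step 2 for an event that needed a significant intervention but posed no danger to life.

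**Size.** Let F be the number of adverse events graded on the fallback scale. The number wrongly labelled life-threatening lies between 0 and F. The protocol gives no adverse event rate, no admission rate and no share of events that CTCAE cannot grade, so F is unknown and may be 0.

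**Between arms.** One scale serves both arms, and section 3.3 keeps the investigator responsible for follow-up blinded. Nothing in the protocol shows that the mislabelling would fall more on one arm.

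**The case against.** The strongest case against is that this is loose wording with little consequence. Several parts of that case stand.

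- **Scope.** CTCAE version 5.0 governs all events, and the local scale is an exception. A reader might infer that severity is inflated across the trial. The protocol supports only that it can be inflated for events CTCAE cannot grade.
- **Regulatory route.** Section 8.6 sets its fastest clock "without delay for serious adverse unexpected fatal or life-threatening", against 15 calendar days for other serious effects. A reader might infer that a fallback Grade 4 puts an event on the wrong clock. Nothing in 8.6 ties the clock to the grade. It is worded in terms of seriousness and expectedness, and seriousness is recorded separately from intensity.
- **Notice to the sponsor.** Grades 3, 4 and 5 all trigger the same immediate notice, and an event needing admission is normally an SAE reportable within 24 hours anyway, apart from the listed exceptions. Little changes here.
- **Loss of work.** Section 5.7 says "Labor activity is suspended for one week", and loss of work appears in Grade 3, so a reader might infer that any event in the first week becomes severe. That does not follow. The Grade 3 descriptors are separated by semicolons without *or*, the scale grades the intensity of the event, and the week off is routine post-treatment care that no adverse event caused. It raises no grade.
- **Use in analysis.** The restatement in section 8 names number, type and distribution by arm, and the table in 7.3 has no grade column. Severity as a safety measure rests on 2.4.2 alone.

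None of this removes the conflict between the fallback Grade 4 descriptor and 8.2, and 2.4.2 is the endpoint definition.

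**Conclusion.** The point holds in a narrow form. The fallback scale in 8.5 labels an event life-threatening on the strength of an admission or a significant intervention alone, while 8.2 treats threat to life and hospitalisation as different things. Applied as written, it can overstate severity, a safety measure named in 2.4.2.

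The effect is limited to events that CTCAE cannot grade. Its size cannot be derived from the protocol and may be zero, and no bias between arms is shown. A reader might try to size it by applying an assumed admission rate to the 52 patients: at 5% to 10%, 52 × 0.05 = 2.6 and 52 × 0.10 = 5.2. That would require every admission to be both ungradable by CTCAE and free of threat to life. The protocol supports neither step, nor the rate itself, so the figure should not be used.

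The conclusion assumes that investigators apply the descriptor rather than the label when the two disagree. The text does not say which governs, and that is part of the fault.

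**What to change.** Reconcile 8.5 with 8.2:

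1. Define fallback Grade 4 as an event that is life-threatening in the sense of 8.2.
2. Remove hospitalisation and significant clinical intervention as conditions that are enough for Grade 4.
3. State that an ungradable event needing admission or intervention without threat to life is graded by its intensity, at most Grade 3, and that the hospitalisation is recorded as a seriousness criterion under 8.2.

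The third step is needed because deleting the present descriptor alone would leave such events without a clear grade. No change to the Grade 3 wording or to 5.7 is needed for this point. The cost is a short protocol rewording, a revised AE form and brief retraining of those who complete it.
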